### Intervention: PCT

All participants will receive 8 weekly individual PCT sessions with a duration of 45 minutes each administered by a trained licensed therapist from Amsterdam UMC. PCT is based on the model by Beck [51] and specifically designed for relapse prevention [28,29,42]. Each session consists of a structured format, starting with homework review and explanation of the sessions’ rationale and ending with homework assignments. Homework is an essential part of the therapy and will take 10 minutes each day at most. The treatment is based on the PCT manual [27-29,32].

The number of attended sessions, the overall time taken by the sessions, and whether homework was done will be monitored. All concomitant care will be allowed during the intervention, but if patients are no longer in remission during treatment, they will be noted as relapsed and withdrawn from the study and then referred to their treating psychiatrists for further treatment options. The date of relapse will be noted and used in the analysis of our secondary outcomes.

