#### Secondary Outcomes

Affect fluctuations are the second study parameter and will be measured using a daily short-form questionnaire (via ESM), including the visual analog mood scale and questions on positive and negative affect [53-55]. Participants will complete the daily questionnaire on their affective state during PCT, from which the mean affect score will be calculated. To increase compliance with the ESM questionnaires, 3 strategies will be used in this study. First, the days in which participants receive the ESM questionnaires will be fixed and customized to the preference of each participant in consultation with the outcome assessor. Second, reminders to fill out the ESM questionnaires will be sent via email when compliance is low. Third, patients will be instructed to complete the ESM questionnaires as quickly as possible to minimize retrospective memory distortion. Low-responding individuals will also be included in the analysis.

To determine the remission period, the number of weeks of remission will be monitored using the IDS-SR [56] and HDRS-17 [57]. Relapses will be identified by the treating therapist. Both questionnaires will be used for registering depressive symptoms and response rates to rTMS (treatment as usual) and administered directly after completing PCT and 3 and 6 months after baseline.

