#### Statistical Analysis of the Secondary Objectives

To explore changes in affect fluctuations and the duration of a remission period, several statistical methods will be used. Repeated linear mixed models will be used if normality is reached to compare variation in individuals’ affective states over time in the intervention groups. Participants will be included as a random intercept. If applicable, demographic characteristics such as sex and age will be used as covariates. A survival analysis (ie, Kaplan-Meier curve) will be used to compare the time to depressive relapse (as assessed using the IDS-SR and HDRS-17) overall and between the 2 study groups. Finally, to identify the optimal course of therapy in a larger future RCT, the descriptive results of the secondary parameters will be qualitatively illustrated.

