rTMS as a treatment for MDD has had response rates ranging from 40% to 50%, with approximately 30% of responders achieving remission [18,58]. However, sustaining these beneficial outcomes presents a challenge. While one study reported a response rate of 43.6% at 1 year after rTMS treatment [59], another study observed a response of merely 22.6% at 6 months after rTMS treatment [21]. A common strategy to sustain these positive effects is to provide maintenance rTMS [60,61]. However, maintained rTMS in depression has some disadvantages, such as being time-consuming; 37.8% of the patients relapsing within 20 weeks; and long-term treatment being linked to different side effects, including difficulty sleeping and headaches [62,63]. Therefore, a different strategy for relapse prevention after successful rTMS treatment is needed. PCT offers a relatively brief treatment course focused on relapse prevention in patients with MDD, with demonstrated long-term efficacy [22,33-37]. In this pilot study, we will offer PCT either face-to-face or online to patients who have recently effectively finished rTMS treatment to establish the feasibility of the different delivery formats for a larger RCT on the efficacy of administering PCT after rTMS. To our knowledge, this is the first study to provide PCT immediately following rTMS. Other strengths of this study include the extensive measurement of treatment adherence and daily measurement of affect as earlier research has established fluctuations in affect as predictors of depression relapse [7,8]. A limitation of this study is that it is single-blinded as the participants are aware of their group allocation. To minimize related bias within this study, a blinded outcome assessor will conduct all questionnaires, and participants are instructed not to tell this assessor their treatment allocation.

In conclusion, the findings of this pilot study may enhance our means to study an add-on treatment strategy for promoting remission as well as relapse prevention in patients with MDD after successful rTMS treatment and likely increase treatment adherence in an RCT on the effectiveness of PCT following rTMS treatment as a prevention strategy.

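### Three passages disagree on what counts as relapse in the time-to-relapse comparison, and the scale visits locate a relapse only to within about 5 to 13 weeks

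*Protocol article*

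**What the plan says.** Three places in the protocol article bear on the relapse event.

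- **Secondary Outcomes:** "Relapses will be identified by the treating therapist". No instrument or threshold is attached to that judgement. The same section measures weeks in remission with the IDS-SR and HDRS-17, which are "administered directly after completing PCT and 3 and 6 months after baseline".
- **Statistical Analysis of the Secondary Objectives:** a Kaplan-Meier curve is to "compare the time to depressive relapse (as assessed using the IDS-SR and HDRS-17) overall and between the 2 study groups".
- **Intervention: PCT:** "if patients are no longer in remission during treatment, they will be noted as relapsed and withdrawn from the study", and "The date of relapse will be noted and used in the analysis of our secondary outcomes".

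Table 1 schedules neither scale between baseline and the end of PCT; only the affect form and the outcome rating scale are given in that period. On blinding, the Discussion relies on the arrangement that "a blinded outcome assessor will conduct all questionnaires". The Outcomes overview says that every questionnaire except the HDRS-17 is self-reported.

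**The concern.** One time-to-event endpoint has more than one possible source, and the article does not say which prevails. The sources differ in three ways that matter to a comparison of formats.

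- **Who judges.** A therapist who delivers the allocated format necessarily knows it, and sees one arm by video and the other in person. A relapse called by that person falls outside the blinded assessment that the Discussion offers as protection against bias.
- **When they can see the patient.** PCT is 8 weekly sessions, while follow-up runs to 6 months.
- **How the event is dated.** In-treatment relapses get a noted date. Relapses found by the scales are known only to fall between two visits.

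The Discussion adds that if neither adherence nor efficacy differs, participant preference alone should decide the format. The relapse comparison therefore has some bearing on the advice for the larger trial.

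**Working it through.** There is no planned figure to reproduce: the sample size of 20 rests on practicality, with no event count or effect size.

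**1. Coverage by source and period**

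- *Baseline to T1 (about week 8):* no scale is scheduled. The only information is a relapse noted and dated during PCT. That participant is withdrawn, so a T1 scale cannot be assumed.
- *T1 to T3 (about week 8 to week 26):* the scales are given at T1, T2 and T3. If the treating therapist is the PCT therapist, no contact is scheduled in this period.

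Under that reading each source covers what the other misses. A curve using both changes its event definition at about week 8.

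**2. Precision of a scale-detected date**

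Taking 3 months as 13 weeks and 6 months as 26 weeks, the gaps are:

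- baseline to T1: 8 − 0 = 8 weeks
- T1 to T2: 13 − 8 = 5 weeks
- T2 to T3: 26 − 13 = 13 weeks

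After PCT a scale-detected relapse is therefore located to within 5 or 13 weeks. A count of weeks in remission cannot be read from that. T1 follows the end of PCT, so if PCT overruns, the first gap lengthens and the second shortens.

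**3. What dating at the visit would do (illustration only)**

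The article does not say that follow-up relapses are dated at the visit; this step assumes it. Relapse times were simulated with a constant hazard in each 13-week half and moved to the next visit.

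- With remission of 60% at 3 months and 22.6% at 6 months (one study cited in the Introduction), the hazards are −ln(0.60)/13 = 0.0393 and −ln(0.226/0.60)/13 = 0.0751 per week. The true median is 13 + (0.693 − 0.511)/0.0751 = 15.4 weeks; the visit-dated median is 26. The mean delay is 5.5 weeks.
- With two assumed milder patterns (80%/60% and 90%/75%), the mean delay is 5.2 and 5.4 weeks.

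The size of the delay is driven mainly by the visit gaps and varies little with the relapse rate.

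**4. Weight of a single event**

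The same three patterns give 11 × 0.25 = 2.8, 11 × 0.40 = 4.4 and 11 × 0.774 = 8.5 expected relapses among 11 participants. The split by arm is not reported. If it is 5 and 6, one event classified differently moves an arm's proportion by 1/6 = 17 to 1/5 = 20 percentage points; if 4 and 7, by 1/7 = 14 to 1/4 = 25 points.

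**The case against.** **The therapist may not be the PCT therapist.** The consent section uses treating psychiatrists, therapists and other providers for clinicians who screen patients, and the Safety section calls the PCT provider the PCT psychologist. Concomitant care is allowed throughout. A reader might infer that no therapist can see a relapse after week 8, or that every therapist-called relapse is unblinded. The documents do not establish either; both depend on who is meant. This stands, and it adds to the need to name the source.

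**Relapses are dated.** The Intervention section provides for a noted relapse date, so calling events generally mis-dated goes too far. That stands for the treatment period. For follow-up, the scale schedule cannot supply an exact date, whatever rule a fuller document may contain.

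**A relapse rate from the literature.** A reader might compute (60 − 22.6)/(100 − 22.6) = 48% from the cited study and report it as the share of this trial's relapses occurring after month 3. It is not a trial figure: it comes from one study, is timed from the end of rTMS, and is not a planning assumption. The Discussion itself sets the 22.6% beside 43.6% at 1 year in another study.

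**Blinding is not wholly lost.** Questionnaires remain with the blinded assessor. Equally, the IDS-SR is completed by participants who know their format, so the scales were never a fully blinded pair; the HDRS-17 is the assessor-rated one.

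**Kaplan-Meier may be good enough.** Both arms share one schedule, so visit dating does not by itself favour an arm. With complete visits, a purely visit-dated curve gives the same values at T1, T2 and T3 as simple proportions. That is right, and is why a clearly labelled visit-dated curve is acceptable. It does not cover a curve that mixes noted dates with visit dates.

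**Detail belongs in the analysis plan.** A cut-off or dating rule may well be there, and its absence here is not the point. The article itself states conflicting event sources.

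**Conclusion.** The conflict is in the text: the Intervention, Secondary Outcomes and statistical sections do not agree on what makes a relapse in the time-to-relapse comparison. Scale-detected relapses after PCT are known only to within about 5 to 13 weeks, so the scales alone cannot give weeks in remission, and a mixed curve would be inconsistently dated. The visit gaps follow from the schedule. The mean delay of 5.2 to 5.5 weeks holds only if events are dated at visits and the assumed relapse patterns are roughly right. The blinding concern rests on the likely but unstated reading that the treating therapist delivers PCT.

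The impact is limited. This is a secondary, descriptive outcome in a pilot with 11 participants, and the adherence outcome is untouched. A reader might infer that the between-format relapse result is biased towards one arm; nothing in the documents shows a direction. The change should still be made, because it is cheap and one event carries a lot of weight at this size.

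**What to change.** Before unblinding, reconcile the three passages for the analysis endpoint:

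- Name the blinded HDRS-17 at T1, T2 and T3, against one pre-specified cut-off, as the main relapse source, with the IDS-SR supportive. Since partial responders are eligible, the definition must work for someone not in full remission at baseline.
- Count a relapse noted during PCT that led to withdrawal before T1 as an event in the baseline-to-T1 interval. State how many events rest on that source, which is unblinded if the PCT therapist made the call. One source cannot serve alone, because these participants may have no T1 scale.
- Present the proportion relapsed by T1, T2 and T3 per arm with exact confidence intervals. Analyse any curve as interval-censored (for example a Turnbull estimate) or label it as visit-dated.
- Say who the treating therapist is. Leave the clinical withdrawal rule as it stands, apart from bringing its wording into line with the other two passages.

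The article reports that analysis had not started as of June 2026. If unblinding has since occurred, the choice should be declared as made afterwards. The cost is a few lines of text and a standard routine, with no new data. What is given up is exact-looking relapse dates, and a relapse that begins and resolves between visits can be missed.

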#### Exploratory Outcomes

There are no exploratory outcomes in this study.

### Statistical Analysis

All randomized participants will be included in the analysis and assessed by intervention group.

#### Statistical Analysis of the Primary Objective

For our primary outcome of feasibility of the different PCT formats, no difference in treatment adherence between both intervention groups is hypothesized. The data on PCT sessions followed, outcome rating scale, and homework assignment compliance will be qualitatively described to determine the best possible treatment options for a larger RCT. Missing data (eg, percentage of missed questionnaires) will be included in the description of adherence. The rate of recruitment and completion of therapy will also be qualitatively described as an indicator of feasibility of the study itself.

#### Statistical Analysis of the Secondary Objectives

To explore changes in affect fluctuations and the duration of a remission period, several statistical methods will be used. Repeated linear mixed models will be used if normality is reached to compare variation in individuals’ affective states over time in the intervention groups. Participants will be included as a random intercept. If applicable, demographic characteristics such as sex and age will be used as covariates. A survival analysis (ie, Kaplan-Meier curve) will be used to compare the time to depressive relapse (as assessed using the IDS-SR and HDRS-17) overall and between the 2 study groups. Finally, to identify the optimal course of therapy in a larger future RCT, the descriptive results of the secondary parameters will be qualitatively illustrated.

### Privacy and Confidentiality

All study and medical data will be handled confidentially in accordance with the European Union (EU) General Data Protection Regulation and the Dutch General Data Protection Regulation Implementation Act. All participant data will be securely stored using a coded participant ID number. Informed consent forms will be stored separately from the participant ID-coded study records (eg, the clinician-rated HDRS-17 forms) in a locked file cabinet to which limited access is guaranteed. Only staff members (eg, clinical interns and clerical personnel) authorized by the principal investigators, the monitoring agency of Amsterdam UMC, and the Health and Youth Care Inspectorate will be allowed access to the original documents. All electronic databases are password protected and stored securely on a local Amsterdam UMC drive. Data collection will mostly take place via direct entry into Castor Electronic Data Capture. The videoconferencing program that will be used is built into Epic (ie, telehealth) and thereby creates a secure line directly to the participants. No digital information on the PCT sessions will be stored (ie, sessions will not be recorded), and it will be ascertained that the correct videoconferencing program is used for communication between participants and therapists. This will ensure participants’ privacy during online treatment.

Data will be stored for 15 years within Amsterdam UMC in accordance with Dutch guidelines.

Coded data may be used for other research on rTMS and/or PCT. Participants need to provide informed consent prior to the use of their data in other research (as an opt-in item on the informed consent form). Storage for 15 years will be applied. Coded data will be shared with other sites on reasonable request for noncommercial research purposes. Coded data could be sent to countries outside of the EU where other privacy regulations are in place. Non-EU countries will only receive coded data preserving participant privacy to the best of our ability. If data are shared, they will be fully coded in accordance with Dutch privacy regulations.

### Ethical Considerations

#### Overview

This study was reviewed and approved according to the Medical Research Involving Human Subjects Act (WMO; *Wet Medisch-Wetenschappelijk Onderzoek met Mensen*) by the MREC of Amsterdam UMC on June 17, 2024. Additionally, the trial was registered in the Dutch National Trial Register (trial registration NL85703.018.23) on November 10, 2023. Important protocol modifications will be notified to the MREC.

#### Informed Consent

Any questions will be answered by the researcher before obtaining consent. Written informed consent will be obtained freely and voluntarily prior to enrollment and participation in the baseline assessment. This informed consent form will additionally be signed and dated by the outcome assessor. Participants will receive a copy of the signed informed consent form, and their health care specialist will be informed about participation in the study. The informed consent form will include an opt-in item for using the participants’ data for other research on depression and/or PCT.

#### Participant Compensation

Participants will receive reimbursement for necessary travel expenses, parking fees, and/or telephone costs.

#### Withdrawal

Participants can leave the study at any time for any reason if they wish to do so without any consequences. If participants withdraw after inclusion, this will be noted as a dropout, but continuation of their PCT will be possible without taking measurements.

#### Monitoring

The Clinical Monitoring Center of Amsterdam UMC will monitor the study procedures and storage at the start of the study and throughout the duration. This is in accordance with the guidelines of the Dutch Federation of University Medical Centres and complies with the applicable laws and regulatory requirements (eg, WMO and International Council for Harmonisation of Technical Requirements for Pharmaceuticals for Human Use good clinical practice). During this study, 2 on-site visits and 1 remote monitoring visit will be performed.

#### Safety

Adverse events and serious adverse events reported spontaneously by the participants or observed by the investigator or his staff will be recorded in accordance with the applicable laws and regulatory requirements (eg, WMO and good clinical practice). Adverse events will be defined as undesirable experiences occurring to a participant during the study when related to PCT. Serious adverse events will be reported to the MREC of Amsterdam UMC. No data safety monitoring board has been appointed due to negligible risks of the added PCT on top of regular care.

If acute psychiatric illness (eg, acute suicidality identified via the HDRS-17 or IDS-SR questionnaire or observed by the PCT psychologist) is identified during the study, the participant will be advised to contact their (mental) health care professional or general practitioner (GP) or an out-of-hours GP service. In case of a crisis, the health care professional or GP can consult a psychiatrist or refer the participant to a local crisis center. If a participant refuses to seek help for acute suicidality, the involved researchers will assess the risk of suicidality and determine whether the researchers themselves need to contact the GP, health care professional, or crisis center.

There are no provisions for ancillary and posttrial care as it is expected that participants will be in remission or still have access to their care system related to depression prior to rTMS, which will follow up on necessary care. The liability insurance of the investigator applies to damage that becomes apparent during the study or within 4 years after the end of the study.

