### Randomization and Blinding

In total, 20 participants will be randomized with a 1:1 allocation ratio to PCT online or face-to-face. A computer-generated randomization table with small block sizes stratified by gender will be used by an independent researcher. After randomization has taken place, an independent researcher (who is not blinded to treatment allocation and will not conduct outcome assessments) will contact the participants and related health care professionals to communicate the participants’ treatment allocation to start the PCT sessions. Participants will be instructed not to share treatment allocation with the blinded outcome assessor. This is to ensure that outcome assessors remain blinded until the end of data collection and consequent database lock.

If knowledge of the allocated group is necessary for the safety of the patients or providing medical treatment, unblinding will be performed by the treating psychologist or the previously mentioned independent researcher.

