## Results

This study was funded in November 2023 by the Netherlands Organisation for Health Research and Development. Data collection started in August 2024. As of September 2025, participant recruitment has concluded with a total of 11 participants. In April 2026, the last follow-up measures were performed, and data collection ended. As of June 2026, data analysis has not started. We expect data analysis and publishing of results to be completed in the fall or winter of 2026. The study findings will be disseminated through publication in peer-reviewed scientific journals, as well as presentations at relevant platforms such as clinical care meetings where appropriate.

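### The adverse event definition requires relatedness to PCT, so a low count would describe only events that someone attributed to PCT

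*Protocol article*

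**What the plan says.** The Safety section of the protocol article first sets out how events are collected: "Adverse events and serious adverse events reported spontaneously by the participants or observed by the investigator or his staff will be recorded", in line with the applicable rules. The next sentence fixes what counts: "Adverse events will be defined as undesirable experiences occurring to a participant during the study when related to PCT". For serious events it says "Serious adverse events will be reported to the MREC of Amsterdam UMC", with no definition and no relatedness condition of their own. The section then explains the oversight arrangement: "No data safety monitoring board has been appointed due to negligible risks of the added PCT on top of regular care".

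The section does not say who judges relatedness, by what criteria, or whether events judged unrelated are logged anywhere.

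Both arms receive the intervention: "All participants will receive 8 weekly individual PCT sessions" (Intervention: PCT). The plan was that "In total, 20 participants will be randomized with a 1:1 allocation ratio to PCT online or face-to-face" (Randomization and Blinding). The Results section reports that "participant recruitment has concluded with a total of 11 participants", that follow-up ended in April 2026, and that analysis had not started as of June 2026.

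**The concern.** In a safety record one normally notes what happened and then, as a separate step, whether the intervention may have caused it. Here the causal opinion comes first and decides whether the event counts as an adverse event at all. An event put down to the underlying depression drops out of the adverse event list, and a later reader cannot see that it occurred or disagree with the attribution.

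This matters more here than in a routine use of PCT, on the article's own account. The Introduction says that PCT is normally offered no earlier than 10 weeks into remission, whereas here it follows rTMS as soon as possible and includes partial responders. It names the intensity of the combined treatment as a major concern. The Discussion says that, to the authors' knowledge, no earlier study has given PCT immediately after rTMS. The Introduction also cites a study in which 22.6% of rTMS responders were still in remission at 6 months. Undesirable events that could be ascribed to the illness are therefore foreseeable, and PCT's contribution would be hard to judge case by case. The expectation of negligible risk could itself influence what is judged related.

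What is at stake is how a short or empty adverse event list is read when the larger trial is planned.

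**Working it through.** The article states no adverse event rate or other figure on this point, so there is nothing to reproduce. The check is a reading of the text, followed by arithmetic on what a count would mean.

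**1. Does any other text undo the condition?**

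- *Recording sentence (Safety).* It covers adverse events, but the following sentence defines the term. Read together, what is recorded under that name is what was judged related.
- *Relapse (Intervention: PCT).* Relapse and its date are noted regardless of cause, as an outcome.
- *Symptom scores (Table 1; Secondary Outcomes).* HDRS-17 and IDS-SR are scheduled at baseline, after treatment, and 3 and 6 months after baseline, regardless of cause. The cover is incomplete: participants who relapse during treatment are withdrawn, and those who withdraw may continue PCT without measurements (Withdrawal).
- *Dropout (Withdrawal).* It is noted regardless of cause.
- *Acute suicidality (Safety).* It triggers a referral pathway regardless of cause, but the text does not say that it is entered as an adverse event.

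So depression-related harm is partly visible elsewhere. Other undesirable events judged unrelated have no stated place in the record.

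**2. What would zero adverse events mean?** With 0 events in n participants, the exact (Clopper-Pearson) upper limit is 1 − (α/2)^(1/n) two-sided and 1 − α^(1/n) one-sided, with α = 0.05.

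| n | Two-sided 95% | One-sided 95% |
|---|---|---|
| 11 (enrolled) | 1 − 0.025^(1/11) = 28.5% | 1 − 0.05^(1/11) = 23.8% |
| 20 (planned) | 1 − 0.025^(1/20) = 16.8% | 1 − 0.05^(1/20) = 13.9% |

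Under the stated definition, these limits apply to the proportion of participants with an event judged related to PCT. They say nothing about all untoward events.

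**3. How far could the condition thin the list?** Let p be the probability that a participant has an undesirable event and q the share of such events judged related. Neither is in the article; the values below are assumptions, with at most one event per participant and independence between participants. The expected number recorded is n·p·q, and the chance of at least one is 1 − (1 − p·q)^n. For n = 11:

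| p | q | Expected recorded | Chance of at least one |
|---|---|---|---|
| 10% | 1 (no condition) | 1.10 | 0.69 |
| 10% | 0.5 | 0.55 | 0.43 |
| 10% | 0.1 | 0.11 | 0.10 |
| 20% | 1 (no condition) | 2.20 | 0.91 |
| 20% | 0.5 | 1.10 | 0.69 |
| 20% | 0.1 | 0.22 | 0.20 |

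For example, with p = 10% and q = 0.5: 11 × 0.10 × 0.5 = 0.55, and 1 − 0.95^11 = 0.43. An empty list thus has probability 0.31 without the condition (1 − 0.69), 0.57 at q = 0.5 and 0.90 at q = 0.1, for the same underlying rate of events.

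**The case against.** The strongest reply is that this is a feasibility pilot. Safety is neither an objective nor an outcome, no safety comparison between arms is planned, and negligible risk is the stated reason for having no monitoring board, not a hypothesis under test. The harms most likely in this population are largely captured as relapse, dropout and symptom scores. All of this stands, and it limits the weight of the point.

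Four stronger readings are tempting, and the article does not support them.

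- *That nothing is recorded until causality is judged.* This goes too far, given the data collected regardless of cause. The condition governs what is called an adverse event.
- *That serious adverse events are filtered in the same way before they reach the ethics committee.* That sentence has no relatedness wording. The condition would reach serious events only if they are read as a subset of adverse events as defined. A separate definition may well stand in the full protocol, which is not shown.
- *That relatedness is judged by people who know the allocation.* No judge is named. Participants and the treating psychologist know the allocation, but the outcome assessor is blinded until database lock.
- *That the definition is what prevents the trial from testing negligible risk.* With every event recorded, there would still be no arm without PCT, 11 participants, and collection that relies on spontaneous reports and staff observation.

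It might also be said that the reference to legal requirements and good clinical practice implies fuller recording. The article does not say so, and its own definition is explicit. None of these replies restores events judged unrelated to the adverse event record.

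**Conclusion.** The point holds as one about the definition and how the resulting count is read. The article states a rule, and nothing else in it corrects that rule: an undesirable event judged unrelated to PCT is not an adverse event, and the judgement cannot be checked from the adverse event record. A low count would describe only events attributed to PCT. For 0 of 11 the two-sided 95% upper limit on that attributed rate is 28.5%. The limit is valid for those events, but is no evidence about all untoward events and should not be used as such when the larger trial is planned.

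How many events the rule removes cannot be known from the article. The figures for p and q are illustrations under assumed values. No sample size or planned analysis depends on the definition, so the severity is moderate: worth correcting, without threatening the primary objective.

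**What to change.** Define an adverse event as any undesirable experience during study participation, whether or not it is considered related to PCT, and record relatedness and seriousness as separate fields. This wording should also go into the protocol of the larger trial.

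Rewording cannot change what was collected up to April 2026. For this pilot, before analysis starts, the sponsor should:

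1. list all untoward events recoverable from study notes and the electronic health record, which the article already names as a source for adherence data, within existing consent;
2. report them descriptively by arm, with the subset judged related shown separately;
3. state in the report that events judged unrelated at the time may be missing, including any never reported or treated elsewhere.

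The cost is a sentence in the Safety section, notification of the ethics committee if the change counts as an important modification, and a short record check for 11 participants. The downside is a longer list that includes events of the underlying illness; the separate relatedness field lets the reader see which these are. The change makes the safety record more complete and open to checking, but will not by itself demonstrate negligible risk.
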